### 2.4. Study Sample

The subjects will be recruited at the Ramon and Cajal University Hospital Rehabilitation Unit in Madrid (Spain). Those diagnosed with Stroke who attend the unit will be referred to a Physical Therapist, a member of the research team, who will check the inclusion and exclusion criteria, before inviting them to participate in this study.

The inclusion criteria are subjects diagnosed with Stroke between 6 and 24 months before starting this study, over 50 years old. The exclusion criteria are subjects who present moderate or severe cognitive impairment according to the Pfeiffer Questionnaire [31], have other serious diseases with a significant impact on functional capacity, and suffer a previously diagnosed psychiatric pathology or were dependent with regard to basic activities of daily living before suffering the Stroke.

Potential participants will be provided with all the relevant information through the information form and further verbal explanation. They will be told that they will be randomly allocated either in the experimental or control and that each group will be treated with different PT techniques appropriate for their condition, and that the aim of this study is to determine the best results. The patients will not be informed about which group they are assigned. If they decide to participate, they will be asked to sign the informed consent form and, afterwards, 2 Physical Therapists, members of the research team, will carry out the baseline assessment.

### 2.5. Randomization and Blinding

Once the inclusion and exclusion criteria are revised, and after every participant signs the informed consent, participants will be included in this study and codified with a number from 0 to 62.

Randomization will be computer-generated by the statistics program Epidat v.4.1 (La Coruña, Spain) with a 1:1 proportion to the experimental group (EG) or control group (CG). This assignment will be blinded to the assessor.

Only the Physical Therapists who will carry out the interventions will have access to randomization.

### 2.6. Study Flow

After randomization, sociodemographic, clinical, and outcome variables will be collected at baseline assessment (A0). PT interventions will be carried out in each group for 10 weeks. After group interventions, an intermediate assessment (A1) will be performed, and a follow-up assessment (A2) will be carried out 6 months after A0.

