### 2.7. Outcome Variables

Outcome variables will be collected at 3 points: at baseline (A0), at the end of the group interventions (A1), and 6 months after baseline (A2). The assessments will be carried out by 2 Physical Therapists, members of the research team, after training and consensus meetings. The assignment will be blinded to the two physical therapist assessors. Sociodemographic variables (Table 1) are age, sex, duration of Stroke, work status, type of Stroke, affected hemibody and comorbidities.

*Primary variables* (Table 2) are as follows:-Quality of Life: Measured with the Spanish version of Newcastle Stroke-Specific Quality of Life Measure (NewsQoL), developed by Buck et al. [32] to measure the quality of life of people after a Stroke. It consists of 56 items distributed in 11 dimensions. The range of scores varies from 0 to 3 points for each of the items. In each dimension, a result is obtained from 0% to 100%, with a higher score representing a worse perception of quality of life. It is adapted and validated in the Spanish population [33] and it has proven to be sensitive and reliable [34].-Participation: Measured with the Oxford Participation and Activities Questionnaire (Ox-PAQ), an instrument for measuring participation and activity levels based on the International Classification of Functioning, Disability and Health (ICF) [35]. It consists of 23 items divided into 3 dimensions: routine activities, social commitment, and emotional well-being. Each item is scored on a Likert scale from 0 to 4 points. Higher results mean greater difficulty in participation [35]. It is valid for people who have suffered a Stroke [36], and the Spanish version is up to be done.-Functionality: Measured with the modified Barthel Index [37], used to assess the functionality of activities of daily living of people with neuromuscular and/or musculoskeletal pathology, especially in those who have suffered Stroke. The total score ranges from 0 to 100, where 0 indicates complete dependence and 100 indicates complete independence. It is cross-culturally adapted and validated in the Spanish population [38].

**Table 2 jpm-14-00891-t002:** Outcome variables.

Outcome Variables	Assessment Period			Measuring Instruments
	Baseline	Post-Treatment	Six Months after Baseline	
Perception of Quality of Life	x	x	x	NewsQoL-S.V.
Participation in the environment	x	x	x	Ox-PAQ
Functional disability	x	x	x	BI
Gait functionality	x	x	x	FAC-S.V.
Postural control	x	x	x	PASS-S.V.

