#### 2.8.2. Control Group Intervention

Participants assigned to the CG will continue with their standard PT sessions. These sessions will focus on maintaining joint range of motion, practicing transfers from sitting to standing and from standing to sitting, maintaining posture while seated with or without assistance, and performing coordination exercises. Additionally, the CG will engage in activities designed to enhance balance and stability, ensuring a comprehensive approach to preserving and improving functional mobility.

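### Section 2.6 places the whole baseline assessment, GAS goals included, after randomisation; A0 should be complete and the goals locked before allocation

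*Protocol article*

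**What the plan says.** - **Timing of baseline.** Section 2.6 (Study Flow): "After randomization, sociodemographic, clinical, and outcome variables will be collected at baseline assessment (A0". The interventions, A1 and A2 follow.
- **Consent and baseline.** Section 2.4 (Study Sample) describes screening, information and signed consent; "afterwards, 2 Physical Therapists, members of the research team, will carry out the baseline assessment". It does not say whether randomisation falls between consent and baseline.
- **Inclusion.** Section 2.5: "Once the inclusion and exclusion criteria are revised, and after every participant signs the informed consent, participants will be included in this study", with coding and computer-generated 1:1 allocation described next.
- **Access to the allocation.** Section 2.5: "Only the Physical Therapists who will carry out the interventions will have access to randomization".
- **Blinding.** Section 2.5: "This assignment will be blinded to the assessor". Section 2.7: "The assignment will be blinded to the two physical therapist assessors". Section 2.4: "The patients will not be informed about which group they are assigned". Section 2.8 adds that the four treating therapists are blinded to the assessments.
- **What is measured at A0.** Table 2 lists all seven outcomes, including NewsQoL, Ox-PAQ and GAS. Section 2.8.1 says that the tasks trained in the experimental group are aligned with individual functional goals.
- **How A0 is used.** Section 2.9 uses baseline for within-group change, for regression adjustment of baseline differences and, optionally, for ANCOVA.

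**The concern.** A baseline value does its job in a randomised comparison because allocation cannot have affected it. Measuring it before randomisation guarantees this. Measuring it afterwards replaces the guarantee with reliance on blinding.

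Two things are at stake. The first is GAS. Its goals define the scale on which attainment is scored at A1 and A2. If they are chosen when the arm is known, they could differ between arms in difficulty or in how closely they match the training, and a blinded assessor scoring attainment would carry that difference forward. The second is completeness. Someone who leaves after randomisation but before A0 belongs to the intention-to-treat population and yet has no reference value for change or adjustment.

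**Working it through.** The point concerns sequence and access, so the check sets the sections side by side.

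**1. The order of steps.** Section 2.4 gives consent, then A0. Section 2.5 gives eligibility and consent, then inclusion and randomisation. Section 2.6 gives randomisation, then A0, then treatment. One order satisfies all three: eligibility, consent, randomisation, A0, treatment. Baseline after allocation is thus the order the article states.

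**2. Who can know the arm at A0.**
- Treating therapists: yes (Section 2.5), though stated to be blinded to the assessments (Section 2.8).
- The two assessors: no (Sections 2.5 and 2.7).
- Patients: not told (Section 2.4).
- The screening therapist: described only as a research-team member (Section 2.4), and not identified as one of those who treat.

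**3. Exposure by type of measure.**
- Scales scored by the assessors (modified Barthel Index, FAC, PASS, TIS): protected at A0 by assessor blinding.
- NewsQoL and Ox-PAQ, primary in both the Abstract and Section 2.7: the answers come from the patient. The safeguard is that patients are not told their group. It has to hold from randomisation to A0, in patients who have been told that the two groups receive different techniques. The control arm carries on as before (Section 2.8.2: "Participants assigned to the CG will continue with their standard PT sessions"), so news of a change in sessions could reveal the arm. This exposure is small if treatment arrangements are not discussed before A0.
- GAS: least protected. The article does not say who sets the goals. Section 1 describes goal-setting as an interaction between patient and therapist. If the goals that guide training in Section 2.8.1 are the GAS goals, the treating therapists must know that part of A0, and their blinding to the assessments cannot cover it. Whether they are the same goals is not stated.

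**4. Loss between randomisation and A0.** The Abstract gives 31 per arm. One participant lost in that interval is 1/31 = 3.2% of an arm. Section 2.3 allows 10% loss, or 0.10 × 62 = 6.2 participants, without saying when losses occur. The length of the interval is not given, so the expected number cannot be computed.

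**5. Effect of reordering on the sample size.** The inputs in Section 2.3 are d = 0.80, α = 0.05, power 90% and 10% loss. With a two-sample t-test and one-sided α = 0.05 they give 28 per arm, so 2 × 28 = 56, and 56 × 1.10 = 61.6, rounded up to the stated 62. Section 2.3 does not state sidedness, which is a separate matter. The timing of A0 is not an input, so moving it changes none of these figures.

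**The case against.** The strongest reply is that the safeguards are already on paper: those who know the allocation are kept from the assessments, and those who perform or answer the assessments are not told it. For the assessor-scored scales this largely answers the concern. For the questionnaires it answers it as long as patients stay unaware. For GAS it does not, because the source of the goals is unstated and the experimental treatment depends on individual goals.

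It can also be said that the between-group t or Mann–Whitney tests do not need A0, and that Section 2.9 plans intention-to-treat and sensitivity analyses for missing data. That stands: a participant without A0 need not disappear from every analysis. Change from baseline and covariate adjustment would still lack the value.

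Three stronger readings are tempting, and the documents support none of them:
- **That enrolment is steered by a known allocation.** This would need a list visible before enrolment and a treating therapist who recruits. Neither is stated. Eligibility and consent come before inclusion, and restricting access to the treating therapists excludes a recruiter who does not treat. The concealment mechanism may be in the full protocol, which a condensed article need not repeat.
- **That Sections 2.4 and 2.6 contradict each other.** Section 2.4 says only that baseline comes after consent, which also holds if randomisation comes in between.
- **That the bias can be given a figure.** Any figure would rest on an assumed shift and an assumed correlation, neither of which the documents supply.

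**Conclusion.** The point holds as a weakness in the stated sequence. Baseline, including self-reported primary outcomes and individual GAS goals, is recorded after allocation, when the treating therapists can know the arm. The blinding provisions reduce the risk; the main residual exposure is GAS, a secondary outcome, followed by possible losses before A0. The size of any bias cannot be estimated from the article, and no actual influence on baseline values is shown.

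The conclusion assumes that Section 2.6 describes the order that will be followed. If A0 is in practice completed before randomisation, only the text needs correcting. The change is worth making because it is nearly free before enrolment, whereas a baseline already taken after allocation cannot be retaken.

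**What to change.** - Amend Section 2.6 so that the order is eligibility, consent, A0 completed with GAS goals recorded and locked, then randomisation. State the same order explicitly in Section 2.4.
- In Section 2.5, say that each assignment is released to the treating therapist only once that participant's A0 is complete.
- State in Section 2.7 who sets the GAS goals, and that they are not altered for scoring after allocation.

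These steps are already planned; only their order and the release of the assignment change. The cost is minor scheduling effort, since treatment slots are assigned after A0. Sample size, alpha, power and the content of both interventions are unaffected.

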### 2.7. Outcome Variables

Outcome variables will be collected at 3 points: at baseline (A0), at the end of the group interventions (A1), and 6 months after baseline (A2). The assessments will be carried out by 2 Physical Therapists, members of the research team, after training and consensus meetings. The assignment will be blinded to the two physical therapist assessors. Sociodemographic variables (Table 1) are age, sex, duration of Stroke, work status, type of Stroke, affected hemibody and comorbidities.

*Primary variables* (Table 2) are as follows:-Quality of Life: Measured with the Spanish version of Newcastle Stroke-Specific Quality of Life Measure (NewsQoL), developed by Buck et al. [32] to measure the quality of life of people after a Stroke. It consists of 56 items distributed in 11 dimensions. The range of scores varies from 0 to 3 points for each of the items. In each dimension, a result is obtained from 0% to 100%, with a higher score representing a worse perception of quality of life. It is adapted and validated in the Spanish population [33] and it has proven to be sensitive and reliable [34].-Participation: Measured with the Oxford Participation and Activities Questionnaire (Ox-PAQ), an instrument for measuring participation and activity levels based on the International Classification of Functioning, Disability and Health (ICF) [35]. It consists of 23 items divided into 3 dimensions: routine activities, social commitment, and emotional well-being. Each item is scored on a Likert scale from 0 to 4 points. Higher results mean greater difficulty in participation [35]. It is valid for people who have suffered a Stroke [36], and the Spanish version is up to be done.-Functionality: Measured with the modified Barthel Index [37], used to assess the functionality of activities of daily living of people with neuromuscular and/or musculoskeletal pathology, especially in those who have suffered Stroke. The total score ranges from 0 to 100, where 0 indicates complete dependence and 100 indicates complete independence. It is cross-culturally adapted and validated in the Spanish population [38].

**Table 2 jpm-14-00891-t002:** Outcome variables.

Outcome Variables	Assessment Period			Measuring Instruments
	Baseline	Post-Treatment	Six Months after Baseline	
Perception of Quality of Life	x	x	x	NewsQoL-S.V.
Participation in the environment	x	x	x	Ox-PAQ
Functional disability	x	x	x	BI
Gait functionality	x	x	x	FAC-S.V.
Postural control	x	x	x	PASS-S.V.
Dynamic trunk balance	x	x	x	TIS-S.V.
Functional goals	x	x	x	GAS

S.V.: Spanish version; NewsQol: Newcastle Stroke-specific Quality of Life Measure; Ox-PAQ: Oxford Participation and Activities Questionnaire; BI: Barthel Index; FAC: Functional Ambulation Categories; PASS: Postural Assessment Scale for Stroke Patients; TIS: Trunk Impairment Scale; GAS: Goal Attainment Scaling.

Secondary variables (Table 2) are as follows:-Level of gait functionality: Measured with the Spanish version of the Functional Ambulation Categories (FAC). The classification ranges between level 0, which indicates that the subject is unable to walk, and level 5, where the person can walk normally. It was validated in the Spanish population by Viosca et al. [39] and has shown to be sensitive for measuring changes in gait in people who have hemiparesis after suffering a Stroke [40].-Postural control: Evaluated through the Spanish version of the Postural Assessment Scale for Stroke Patients (PASS) [41], a specific instrument to evaluate postural control and balance. The total score varies from 0 to 36 points, with the interpretation being that the higher the score, the better the person’s balance. Validated in the Spanish population in 2015 [42].-Dynamic trunk balance: Measured with the Spanish version of the Trunk Impairment Scale (TIS), developed by Verheyden et al., and adapted to the population with Stroke [43]. It consists of two dimensions: dynamic balance in sitting and coordination. The range of scores varies from 0 to 16 points, with higher scores indicating greater trunk control. It is validated for the Spanish population by Cabanas et al. [44].-Functional goals: Assessed with the Goal Attainment Scaling (GAS), which is a 6-point-scale for measuring significant and realistic functional goals, and demonstrated to be a feasible outcome measure among subacute and chronic Stroke patients [45].

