### 2.3. Sample Size Calculation

Sample size was calculated using G*Power software 3.1.9.7© (Germany) [30]. In order to detect differences in quality of life in favor of the EG, a large effect size of d = 0.80, an error α = 0.05, and a power of 90% were assumed. Considering a possible loss to follow-up of 10%, the sample size results in 62 participants.

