### 2.9. Statistical Analysis

The Statistical Package for the Social Science software (SPSS^®^ v25) for Mac will be used. An intention-to-treat analysis will be performed. Tests will be carried out with a 95% confidence interval and a statistical significance level of *p* < 0.05. First, descriptive analysis will be performed using means and standard deviations or medians and interquartile ranges otherwise. Normality will be studied through Kolmogorov–Smirnov’s test. For nominal qualitative variables, absolute and relative frequencies will be used. The homogeneity of descriptive and baseline data will be analyzed through Student’s *t*-test for independent samples, Welch’s *t*-test, or the Mann–Whitney U-test. In the case of qualitative variables, Pearson’s χ2 or Fisher’s exact test will be used. Baseline differences will be adjusted through covariate adjustment in regression models. ANCOVA might also be performed to control for baseline differences while comparing the means of the outcome between groups.

To analyze within-group differences between baseline, 6-week, and 6-month assessments, repeated-measures ANOVA or Friedman’s ANOVA will be carried out. To estimate the effect size, partial eta squared will be used. On the other hand, to study the differences between groups, Student’s *t*-test for independent samples, Welch’s *t*-test, or the Mann–Whitney U-test will be carried out. The effect size will be estimated using Cohen’s d or following Grissom’s criteria [47,48,49] in the case of the Mann–Whitney U-test.

Finally, the possible effect of the interaction between descriptive data and independent variables (EG and CG) on the dependent variables will be analyzed through ANCOVA, estimating the effect size using partial eta squared.

Intention-to-treat analysis will be performed in order to reduce, among others, the attrition bias and selection bias that could distort the results. Sensitivity analysis will also be performed in order to address the impact of missing data and ensure the results are as reliable and unbiased as possible.

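### Three primary outcomes are tested at p < 0.05 with no hierarchy, adjustment or success rule, while the sample size covers quality of life only

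*Protocol article*

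**What the plan says.** **Primary outcomes.** Section 2.7 lists three primary variables: NewsQoL, Ox-PAQ and the modified Barthel Index, with FAC among the secondary ones. The Abstract has NewsQoL, Ox-PAQ and FAC as primary and Barthel as secondary. All are measured at baseline (A0), after treatment (A1) and six months after baseline (A2). No visit is called primary.

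**Scoring.** For NewsQoL, which has 11 dimensions: "In each dimension, a result is obtained from 0% to 100%, with a higher score representing a worse perception of quality of life". For Ox-PAQ: "It consists of 23 items divided into 3 dimensions: routine activities, social commitment, and emotional well-being". No total is described for either, whereas the Barthel Index is given one.

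**Tests.** Section 2.9: "Tests will be carried out with a 95% confidence interval and a statistical significance level of" p < 0.05. Between-group differences go to Student's t, Welch's t or Mann–Whitney. The section names no visit for these comparisons and gives no hierarchy, adjusted level or success rule.

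**Sample size.** Section 2.3 refers to one outcome: "In order to detect differences in quality of life in favor of the EG". Its assumptions are "a large effect size of d = 0.80, an error α = 0.05, and a power of 90% were assumed", and "Considering a possible loss to follow-up of 10%, the sample size results in 62 participants".

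**Hypothesis.** The Discussion expects the experimental group (EG) to do better on functionality, quality of life and participation. It does not say whether one or all of these must be shown.

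**The concern.** With three primary outcomes, each tested at 5%, and nothing to say how they combine, a reader may take any significant one as proof of effectiveness. The 5% used in planning is then not the error rate of the trial's conclusion.

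The powered comparison is also not a defined endpoint. Section 2.3 treats quality of life as one quantity, section 2.7 describes it as 11 percentages, and no visit is attached to it. The third primary differs between the Abstract and section 2.7, so there are four candidates for three places. Which result is the primary one could be settled after the data are seen.

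**Working it through.** **Inputs from the article:** d = 0.80, α = 0.05, power 90%, 10% loss, N = 62 (31 per group), three primary outcomes, two post-baseline visits. **Assumed, because the article gives none:** correlations between outcomes and between visits.

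**1. The plan's own figure.** Two-sample t-test, noncentral t distribution.
- One-sided α = 0.05: 28 per arm, 56 in total. 56 × 1.1 = 61.6, rounded up to 62, which matches (56 / 0.9 = 62.2, rounded up, gives 63).
- Two-sided α = 0.05: 34 per arm, 68 in total, or 75–76 after loss. This does not match.

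So N = 62 is the size for a single one-sided comparison. Under a two-sided 0.05 test, power is 84% with 28 per arm and 87% with 31.

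**2. Error if any one significant primary counts, one visit.** For k independent two-sided tests, error = 1 − 0.95^k.
- k = 3, independent: 1 − 0.95³ = 14.3%.
- k = 3, simulated multivariate normal (200,000 draws), correlation 0.3 / 0.5 / 0.7: 13.6% / 12.6% / about 11%.

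**3. The same if both visits are tested.**
- k = 6, independent: 1 − 0.95⁶ = 26.5%.
- k = 6, simulated:

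| Correlation between outcomes | Correlation between visits | Error |
|---|---|---|
| 0.3 | 0.5 | 23.8% |
| 0.5 | 0.7 | 20.1% |
| 0.7 | 0.8 | 16.7% |
| 0.8 | 0.9 | 13.6% |

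**4. False results favouring the EG only** (nominal 2.5% per two-sided test).
- Three tests: 1 − 0.975³ = 7.3% if independent; 5.5–6.8% at correlation 0.7–0.3.
- Six tests: 1 − 0.975⁶ = 14.1% if independent; 6.8–12.0% correlated.

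**5. Power if three primaries are kept** (d = 0.80, two-sided).
- Any one suffices, with Holm: the first step uses 0.05 / 3 = 0.0167. Power there is 70% with 28 per arm and 75% with 31. For a given outcome under Holm this is a lower bound, because later steps use larger levels.
- 90% power at 0.0167 needs 44 per arm: 88 in total, and 88 / 0.9 = 97.8, so 98 with loss.
- All three must succeed, d = 0.80 on each, 28 per arm: joint power is 0.836³ = 58.5% if independent and cannot exceed 83.6%.

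**The case against.** **The analysis plan may settle it.** This is a condensed article, and score derivation, primary visit and multiplicity method are commonly left to an analysis plan that is not shown. That stands for the details. It does not cover what the article itself fixes: three primary outcomes, p < 0.05 for the tests, and a sample size for one of them. A correction added later would also change the power stated in section 2.3.

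**Success may require all three.** The Discussion states the hypothesis for the three domains together. If all must be significant, error across them is not inflated. The article does not say so, and step 5 shows that this rule too lowers power.

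**Stronger readings that the article does not support.**
- *A false claim of effectiveness is likely.* False results favouring the EG stay at 5.5–7.3% for three tests at one visit and reach 14.1% for six independent tests. That is above 2.5%, but not likely.
- *NewsQoL has no total score, so it means 11 tests per visit.* The article describes only dimension scores, but it never excludes a total. Section 2.3 and Table 2 treat quality of life as one item. Testing by dimension would raise the error further, but nothing says this will be done.
- *All outcomes are compared between groups at both visits.* The schedule suggests it. Section 2.9 names visits only for the within-group analysis, so the 14–26% range is conditional.
- *The sample size rests on NewsQoL at A1.* Section 2.3 names neither score nor visit, and section 2.6 calls A1 an intermediate assessment.

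The unfinished Spanish Ox-PAQ ("the Spanish version is up to be done") is a separate measurement issue with no bearing on the error rate.

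**Conclusion.** The point holds in limited form. As written, the article has no single primary result that matches its powered comparison, and its stated testing rule does not hold the error of the overall claim at 5%. The size is about 11–14% two-sided at one visit, and about 14–26% if both visits are tested. Both figures assume that any one significant primary counts as success; the ranges span independence down to assumed correlations of 0.7 between outcomes at one visit, and of 0.8 between outcomes with 0.9 between visits over two.

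The gap from the stated 90% power to 70% is not all due to multiplicity. With 28 per arm, moving from a one-sided to a two-sided test takes it to 84%, and dividing α by three takes it from there to 70%.

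**What to change.** Name one primary endpoint that matches the sized comparison: a single prespecified NewsQoL summary score, with its derivation, at one prespecified visit. The choice of summary and visit is the sponsor's, since section 2.3 gives neither. Reconcile FAC and Barthel between the Abstract and section 2.7. Then make participation and that functional measure key secondary outcomes, tested in fixed order or by Holm, with individual dimensions and the other visit as supportive. The six-week assessment mentioned in section 2.9 should also be reconciled with the 10-week schedule.

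If three primaries are kept, state whether one or all must succeed. Under any-one success, apply Holm and restate power from step 5.

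**Cost.** With one primary, the multiplicity fix is a change of wording and needs no extra participants, but participation and functionality lose independent confirmatory status. With three primaries under Holm, either the stated power falls to about 70–75% at the first step, or the total rises to about 98 to keep 90% there.
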